**BACKGROUND**

Acute myocardial infarction (AMI) is often considered one of the main causes of heart failure. Major factors contributing to chronic heart failure (CHF) after AMI include extensive myocardial infarction (MI) and state of coronaries. Death of cardiomyocytes, arterioles, and capillaries in the myocardial infarction area is irreversible and subsequently results in the formation of scar tissue (Orlic D., Kajstura J., et al., 2001). Following remodeling of the left ventricle (LV) leads to progressive dilatation and disruption of its geometry which represents morphological substrate of CHF (Pfeffer MA, Brunwald E., 1990).

During recent years, immune system responses in the presence of myocardial infarction and CHF have been extensively studied. Inflammatory responses and production of cytokine are significantly augmented in AMI leading to remodeling of the heart and following onset of CHF (Nian M., Lee P. et al., 2003). In this regard, primary tasks of modern cardiology consist in recanalization of the infarct-related coronary artery (IRA) and restoration of the myocardial perfusion in patients with AMI. Implementation of various methods of emergency myocardial reperfusion decreased early in-hospital lethality and improved long-term prognosis in these patients. However, CHF, caused by AMI, remains relevant clinical problem.

Transplantation of autologous stem cells is a novel trend in treatment of AMI and prevention of LV remodeling. Prospects for recovery of the myocardium via transplantation of the stem cell with various phenotypes are currently under investigation. Promising results have been generated in various experimental models of ischemic and non-ischemic heart diseases where beneficial effects of transplanted cells were documented. The beneficial effects were mediated by the involvement of the transplanted cells into the myocardial contraction, improvement of mechanical properties of the heart, and paracrine effects of transplantation consisting in the induction of neoangiogenesis (Kocher A.A. et al., 2001, Li R.-K. et al., 1996; Orlic D. et al., 2001; Zhang S. et al., 2003). In these studies, researchers used the following cells for transplantation: embryonic stem cells (ESC), bone marrow stem cells (BMSC), and skeletal myoblasts. Feasibility of cell survival after the transplantation, cell integration into the myocardium of a recipient, and improvement of the cardiac function was confirmed (Сhierchia S., Deferrari L., 2003). Experimental studies on animals showed that bone marrow mononuclear cells (BMMC) can both trigger regeneration of the myocardium in the infarction zone and to trigger myogenesis and angiogenesis with the following improvement of cardiac function (Orlic D., Kajstura J. et al., 2003). The first pilot clinical trials studying the efficacy of BMMC transplantation have been already performed (Hamano K. et al 2001; Strauer B.E., Kornowski R., 2003; Shumyakov V.I. et al.m 2003). However, all these studies were performed at the preclinical stage; the indications and contradictions for administration of this treatment modality have not been unidentified yet. The question regarding optimal time frame for administration of cell transplantation remains unsolved. It is also unclear which type of cells is preferable for the transplantation: ESC, autologous BMMC, CD133+, pure pool of stem cells or the cells that underwent culturing and reprograming. Available literature does not present data on long-term clinical results of cell transplantation in AMI.

The safety and efficacy of autologous bone marrow cell transplantation as well as mechanistic basis of cell transplantation and its effects on cytokines and growth factors in patients with AMI require further studies.

**SUBJECT POPULATION**

The subject population comprises men and women age 18 years and older with STEMI. Each potential subject will have to meet the inclusion criteria and should not be exclusion criteria.

**INCLUSION CRITERIA**

1.​ Age 18 to 75 years,

2.​ Primary STEMI

3.​ Reperfusion time of the infarct-related coronary artery (IRCA) more than 4 h

4.​ Admission at the Coronary Care Unit during the 24 hours after onset of STEMI

**EXCLUSION CRITERIA:**

1.​ Atrial fibrillation, a permanent form

2.​ Valvular heart disease

3.​ Severe comorbidity

4.​ The refusal of the patient to conduct the necessary research

**STUDY DESING**

Single-center, prospective, open, randomized, parallel controlled study.

Planned number of included patients is 90 patients.
Planned date of the inclusion of the first patient is Dec. 1, 2003.
Planned date of the inclusion of the last patient is 20 December 2006.
Planned date of completion of the study is 1 February 2015.
Monitoring of patients will continue until 8 years after suffering a first myocardial infarction.
Basic data from the medical records will be recorded in an individual protocol.

Pts will be randomized to three groups by envelopes: group 1 - pts who will underwent percutaneous coronary intervention (PCI) and ABMMC transplantation; group 2 - pts who will underwent PCI and transplantation of autologous CD133 + bone marrow cells, group 3 - will be comprised pts with only PCI.

**STUDY PROCEDURES**

Patients meeting inclusion and exclusion criteria will be invited to participate in the study. Patient’s consent will be confirmed by signing the written consent form.

Randomization procedure will be conducted by the envelope method after obtaining the written confirmation of patient's consent to participate in the study.

Puncture of the anterior superior iliac spine under local anesthesia will be conducted in patients of groups 1 and 2 4–5 hours before the transplantation of ABMMC or autologous CD133+ bone marrow cells. Bone marrow aspirate (100 mL) will be acquired into two 60-mL syringes containing 10 mL of sterile saline and 25000 IU of heparin. After that, ABMMC and autologous CD133+ bone marrow cells will be isolated by the method of gradient centrifugation (density gradient Histopaque-1077) and separated from erythrocytes, thrombocytes, and granulocytes. We plan to allocate 5–10 • 106 CD133+ BMC and 5-10 • 106 ABMMC. Cellular phenotyping will be performed by the method of flow cytofluorometry (FACSCalibur, Biosciences, USA).

Magnetic labeling with magnetic microgranules CD133 MicroBead (Miltenyi Biotec GmbH, Germany) will be carried out to isolate CD133+ BMC. CD133+ progenitor cells labeled using a hapten-conjugated monoclonal primary antibody and anti-hapten antibody bound to MACS MicroBead microgranules. Positive magnetic separation will be conducted in the separation column in a magnetic field with the device MidiMACS. The purity of cell populations and their viability will be assessed by flow cytofluorometry after immunofluorescent staining with specific CD133/2 (AC141)-PE dye and vital dye 7-AAD by using BD FACSCalibur device (USAVital staining of ABMMC with trypan blue will be used to assess cell viability.

Suspension of 2-4 • 106 ABMMC in 1-mL of heparinized solution (20 U of heparin in 1 mL) will be prepared for transplantation. Intracoronary infusion of ABMMC will be performed by the method of passive passage to the IRA at a rate of 4–8 mL/min. Distribution of 99mTc-HMPAO-labeled mononuclear cells in patient’s body will be studied by scintigraphy (Nuclear Gamma Camera 500, Technicare, USE-Germany).

Plasma samples will be collected to determine serum levels of proinflammatory cytokines and growth factors: tumor necrosis factor α (TNFα), interleukin-1β (IL-1β), hepatocyte growth factor (HGF), vascular endothelial growth factor (VEGF), fibroblast growth factors (FGF), insulin-like growth factors (IGF), and transforming growth factor (TGF) before PCI and 2, 5, and 12 days after the procedure. The levels of cytokines and growth factors will be assessed by enzyme-linked immunosorbent assay: HGF by Biosource (Belgium), VEGF by Cytimmune (USA), FGF by Biosource (Belgium), IGF by DSL (USA), TGF by Biosource (Belgium), IL-1β by Protein contour (Russia), and TNFα by Protein contour (Russia).

**The following clinical parameters will be determined at a time of discharge from a hospital:**

1. Six-minute walk test will be performed to assess the functional class of heart failure. The results will be evaluated according to the criteria of functional classes of the New York Heart Association (NYHA).

2. Functional class of angina will be evaluated according to the classification of the Canadian Cardiovascular Society.

3. The size of myocardial infarction will be determined by counting the index QRS in 12 standard ECG leads by Selvester code to modify Wagner GS et al. (1982).

4. Ultrasound examination of the heart will be held on the ultrasound system VIVID 7, GE Vingmed Ultrasound, Norway.

Patients, enrolled in the study, will be interviewed over the phone 6 months, 12 months, and 8 years after the procedure and will be invited to follow-up visits.

During follow-up visits, we will evaluate the clinical status of patients (the presence of angina, stage and functional class of heart failure, compliance, and quality of life) and the clinical course of cardiovascular disease (complications, the incidence of cardiovascular events, death).

**The following clinical parameters will be determined at follow-up visits:**

1. Quality of life will be assessed using the Minnesota Quality of Life Questionnaire in patients with CHF.

2. Six-minute walk test will be performed to assess the functional class of heart failure. The results will be evaluated according to the criteria of functional classes of the New York Heart Association (NYHA).

3. Assessment of signs of coronary insufficiency will be defined by the presence of stable angina, recurrent myocardial infarction, and unstable angina after myocardial infarction. Evaluation of the functional class of angina will be carried out according to the classification of the Canadian Cardiovascular Society.

4. History of arrhythmias and cardiac conduction defects developed after AMI will be documented.

5. Patient adherence to standard drug therapy will be investigated by the Moriscos-Green test.

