**The following laboratory and instrumental methods of investigation will be carried out during the follow-up visits:**

1. Ultrasound examination of the heart will be performed by using the ultrasound system VIVID 7, GE Vingmed Ultrasound, Norway.

2. Coronary ventriculography will be performed if clinically indicated.

3. Serum BNP levels will be determined with the help of the Triage BNP Test analyzer Triage Meter, Biosite, USA.

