**The following events are defined as safety endpoints:**

1. Clinically significant cardiac arrhythmias including life-threatening arrhythmias.

2. New-onset oncological diseases.

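### Arrhythmia is the first safety end point, but the only item that collects it by name is a history taken at follow-up visits, counted from the infarction, with no stated recording around the infusion

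*Protocol*

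**What the plan says.** The protocol's list of safety end points has two entries, and the first is "Clinically significant cardiac arrhythmias including life-threatening arrhythmias".

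The list of clinical parameters at follow-up visits, item 4, states how arrhythmia is collected: "History of arrhythmias and cardiac conduction defects developed after AMI will be documented".

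The timing is given after the discharge list. Patients "will be interviewed over the phone 6 months, 12 months, and 8 years after the procedure and will be invited to follow-up visits".

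The other places where arrhythmia might have been recorded do not name it:

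- Study Procedures describes the marrow puncture, cell preparation, infusion and scintigraphy. The sentence on the infusion begins "Intracoronary infusion of ABMMC will be performed by the method of passive passage to the IRA at a rate of" and goes on to the flow rate. No rhythm record is mentioned.
- The discharge list contains one 12-lead ECG, and its stated purpose is infarct size: "The size of myocardial infarction will be determined by counting the index QRS in 12 standard ECG leads".
- The laboratory and instrumental list for follow-up visits contains echocardiography, ventriculography if indicated, and BNP.

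Two broader statements could hold some events. Study Design says that basic information from medical records is entered in an individual protocol. The paragraph on follow-up visits says that complications and cardiovascular events are evaluated there. Study Design also describes the trial as open and randomised, with three groups and 90 patients planned.

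**The concern.** The experimental treatment is an intracoronary cell infusion given soon after a STEMI. The hours and days around the infusion matter most for judging whether it provokes arrhythmia. As written, the first point at which the protocol asks about arrhythmia by name is 6 months later, and the question is retrospective.

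Three consequences follow for the safety comparison:

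- **Capture.** A history taken months or years later is likely to miss events. Because the trial is open, what is remembered, volunteered or written down may differ between the cell groups and the control group.
- **Deaths.** A patient who dies before a visit cannot give a history. Death is counted as an end point, but any arrhythmia that preceded it has no stated route into the data. Life-threatening arrhythmia is the part of the end point most exposed to this.
- **Time origin.** The history starts at the infarction, not at randomisation. Arrhythmias that occurred before allocation are counted, although treatment cannot have caused them.

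A statistical analysis plan could change the counting rule, but it could not supply observations that were never recorded. The point therefore belongs in the protocol.

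**Working it through.** The protocol gives no arrhythmia rate, capture rate, alpha or power, so there is no figure to reproduce. The check is a reading of every collection item, followed by an illustration on assumed rates.

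**1. Where arrhythmia is collected**

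| Part of the protocol | Names arrhythmia? | Period fixed? |
|---|---|---|
| Study Procedures (infusion) | No | – |
| Discharge list | No; the ECG is for infarct size | – |
| Follow-up clinical list, item 4 | Yes, as history | From the infarction |
| Follow-up laboratory and instrumental list | No | – |
| Medical-record data (Study Design) | No | No |
| Complications and events at follow-up visits | No | No |

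One source names the end point. Two others may overlap with it, but they fix neither a period nor equal capture across groups.

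**2. Gap between contacts**

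The last interval is 8 years − 1 year = 7 years. Events between infusion and discharge are first asked about by name at 6 months.

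**3. What incomplete capture could cost**

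Assumptions: equal allocation (the ratio is not stated), so 90 / 3 = 30 per group; true risk p; a proportion s of events captured. The chance of recording at least one event in a group is 1 − (1 − s·p)^30.

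| True risk p | s = 1 | s = 0.5 |
|---|---|---|
| 3% | 1 − 0.97^30 = 59.9% | 1 − 0.985^30 = 36.5% |
| 5% | 1 − 0.95^30 = 78.5% | 1 − 0.975^30 = 53.2% |
| 10% | 1 − 0.90^30 = 95.8% | 1 − 0.95^30 = 78.5% |

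For a comparison of two groups of 30 (two-sided alpha 0.05, normal approximation, all assumed), with true risks of 30% and 10%:

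- full capture, 30% v 10%: power 49%
- 75% captured in both groups, 22.5% v 7.5%: power 37%
- 50% captured in both groups, 15% v 5%: power 25%

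Equal under-capture leaves the risk ratio at 3 throughout but removes much of an already limited ability to see it.

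**4. Arrhythmias before randomisation**

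Let b be the risk of an arrhythmia between infarction and randomisation. Randomisation makes b the same in expectation in every group. Let p1 and p0 be the later risks, and assume independence of b. The counted risks are b + (1 − b)p1 and b + (1 − b)p0, so the counted difference is (1 − b)(p1 − p0). It shrinks by the factor 1 − b, and the ratio moves towards 1. This is dilution of any true effect. It does not create a difference where none exists.

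**The case against.** The strongest reply is that silence is not exclusion. The safety end point list does not restrict arrhythmia to the follow-up history. Patients are admitted to a Coronary Care Unit at a single centre, so hospital records exist, and the protocol provides for basic medical-record data. Nor does the follow-up item say that the history is the patient's unaided memory. This stands in part: some in-hospital events may well reach the dataset. What does not follow is that they will do so for a defined period and in the same way in all three groups, because nothing in the protocol requires it.

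Some stronger readings are tempting, and the document does not support them:

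- A reader might infer that arrhythmia will certainly be under-counted, or that nothing is recorded in hospital. The protocol gives no capture rate and leaves the medical-record route open. Likely incomplete capture is as far as the text goes.
- A reader might infer a spurious excess in one arm. With a true 20% in both groups, capture of 90% v 60% would show 18% v 12% (ratio 1.5), but the reverse would show 12% v 18% (ratio 0.67). Both pairs of capture rates are assumptions, and nothing in the protocol favours either.
- A reader might infer that arrhythmias before randomisation bias the comparison. They are balanced in expectation and only dilute it.
- A reader might take the absence of a follow-up ECG as the defect. Resting ECGs at three visits would be up to 90 × 3 = 270 extra procedures, would rarely catch an intermittent or life-threatening arrhythmia, could not fill a 7-year gap, and would be missing for patients who do not attend.

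**Conclusion.** The point holds in a limited form. The first safety end point has one collection item that names it. That item is retrospective, starts at the infarction, and is first applied at 6 months. In an open trial, events around the infusion are likely to be captured late and incompletely, and possibly unequally in an unknown direction. Patients who die before a visit contribute no history. Events before randomisation dilute the contrast.

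The size cannot be derived from the protocol. The losses shown above, such as 78.5% to 53.2% for recording at least one event at a 5% risk, rest on assumed risks, assumed half capture and assumed equal groups of 30. They show how little room a trial of 90 has for losing events. They do not estimate what would be lost.

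No statement in the protocol is wrong or contradicted here. A better method is available from records that should largely exist already, so this is a cheap improvement.

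**What to change.** Three changes to the protocol:

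1. In all three groups, enter in the individual protocol every clinically significant arrhythmia from randomisation to discharge, with date and time, taken from existing ward monitoring and hospital records.
2. After discharge, use hospital and death records as well as the visit history, so that patients who die or do not attend are covered.
3. Count safety events from randomisation rather than from the infarction. This gives all three groups the same starting point, including the control group, which has no infusion. Events between randomisation and infusion remain in the count, as they should in a randomised comparison, and the recorded times allow events after the infusion to be described separately.

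The cost is a small amount of chart abstraction, plus retrieval of hospital and death records after discharge. No extra procedure is needed, and no change to patient management is implied.

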**The following laboratory and instrumental methods of investigation will be carried out during the follow-up visits:**

1. Ultrasound examination of the heart will be performed by using the ultrasound system VIVID 7, GE Vingmed Ultrasound, Norway.

2. Coronary ventriculography will be performed if clinically indicated.

3. Serum BNP levels will be determined with the help of the Triage BNP Test analyzer Triage Meter, Biosite, USA.

**The following events are defined as end points:**

1. Death.

2. Repeated myocardial infarction.

3. Unstable angina.

4. Chronic heart failure (CHF) ≥class II (NYHA).

5. Stroke.

Besides, we will assess the number of planned and emergency admissions to a hospital due to cardiovascular diseases with diagnosis of unstable angina and repeated myocardial infarction.

**The following events are defined as safety endpoints:**

1. Clinically significant cardiac arrhythmias including life-threatening arrhythmias.

2. New-onset oncological diseases.

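### The safety end points include no procedure-specific complication: none for the marrow puncture and, for the intracoronary infusion, only arrhythmia

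*Protocol*

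**What the plan says.** The safety section of the protocol, headed "The following events are defined as safety endpoints", is a closed list of two. The first item is "Clinically significant cardiac arrhythmias including life-threatening arrhythmias" and the second is "New-onset oncological diseases". There is no third item and no general clause for other adverse events.

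STUDY PROCEDURES adds invasive steps for the cell groups. On the marrow harvest it says "Puncture of the anterior superior iliac spine under local anesthesia will be conducted in patients of groups 1 and 2", and 100 mL is aspirated. On delivery it says "Intracoronary infusion of ABMMC will be performed by the method of passive passage to the IRA". That sentence names the mononuclear cells; no route is given for the CD133+ cells. The design section says of the controls: "group 3 - will be comprised pts with only PCI".

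A separate list of main end points contains death, "Repeated myocardial infarction", unstable angina, chronic heart failure of NYHA class II or above, and stroke. It ties none of them to a procedure and sets no time window.

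BACKGROUND closes by naming "The safety and efficacy of autologous bone marrow cell transplantation" among the matters that still need study.

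**The concern.** The cell arms differ from control not only in the cells but in the procedures needed to obtain and deliver them. A patient can be harmed by the puncture (bleeding or infection at the site) or by the infusion (occlusion or dissection of the artery, for example), whatever the cells do. If those harms are not on the safety list and no one is told to look for them during the hospital stay, a report that follows the plan could show similar safety across groups because the relevant events were never counted.

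The trial is also open. Complications written down only when someone thinks to do so may be recorded more fully, or less fully, in the cell arms than in the control arm. A pre-stated item collected in the same way in every group guards against that.

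**Working it through.** The plan states no figure on this point, so there is none to reproduce. The check has two parts.

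**Where each kind of harm would be counted**

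- *Marrow puncture (groups 1 and 2).* Neither safety item fits bleeding or infection at the puncture site, and neither does any main end point. These harms are named nowhere in the protocol.
- *Intracoronary infusion (described for mononuclear cells).* Arrhythmia during or after infusion would count, because that safety item has no limit on cause or timing. Repeated infarction, unstable angina, stroke or death caused by the infusion would count only as a main end point, pooled with up to eight years of ordinary events. Coronary dissection, or an occlusion that causes none of these events, has no place.
- *PCI (all groups).* The position is the same as for the infusion.

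**Whether another part of the protocol fills the gap**

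- The discharge parameters are a walk test, angina class, ECG infarct size and cardiac ultrasound. None is a complication item.
- Blood is drawn before PCI and at 2, 5 and 12 days, but only for cytokines and growth factors.
- Follow-up contacts are at 6 months, 12 months and 8 years. The complications assessed there are those of cardiovascular disease. A haematoma or infection over the iliac spine is not one of them.
- Arrhythmias since the infarction are taken as history at follow-up visits. No peri-procedural check is described.
- The design section says basic data from the medical records go into the individual protocol, but it does not mention complications.

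**What recording would buy**

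Inputs: 90 patients in three groups (protocol, design section). The allocation ratio is not stated. I assume 30 per group, so 30 + 30 = 60 have a puncture.

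With zero events in n patients, the exact one-sided 95% upper limit p solves (1 − p)^n = 0.05, so p = 1 − 0.05^(1/n).

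- n = 60: 1 − 0.05^(1/60) = 1 − 0.951 = 4.9%
- n = 30: 1 − 0.05^(1/30) = 1 − 0.905 = 9.5%

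If allocation were unequal and the two cell groups together held 50 or 70 patients (illustrative values), the limits would be 1 − 0.05^(1/50) = 5.8% and 1 − 0.05^(1/70) = 4.2%.

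The 60-patient figure applies to the puncture only. For the infusion the text supports one group, so the limit for 30 is the one to use unless the CD133+ cells are given by the same route.

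**The case against.** The strongest reply is that much of the serious harm is already collected. The arrhythmia item would pick up an infusion arrhythmia. The main end points include death, repeated infarction, unstable angina and stroke, with no start date that leaves out the hospital stay. A clinically manifest coronary occlusion would largely surface there, and whether it sits under a safety heading is a matter of labelling. Follow-up visits can also look back, as the arrhythmia history does. Finally, the AIM section is about long-term results and does not name procedural safety, and the safety remark in BACKGROUND describes the needs of the field.

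Most of this stands, and it limits the point. A reader might infer that the safety list misses every complication of the cell procedures, or that nothing about their safety could be excluded. The documents do not support that, because arrhythmia, repeated infarction, stroke and death are counted. A reader might also infer that both cell groups have the intracoronary infusion, or that all harms at issue are unique to the cell arms. The text describes the infusion for one cell type only, and group 3 has PCI, which carries its own risk of bleeding, dissection and occlusion. Only the puncture is clearly confined to groups 1 and 2 and stated for both.

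What the reply does not reach is the puncture itself, which no item covers, and the lack of any described assessment around the procedures. Nor can the matter be left to an analysis plan: the protocol itself fixes the safety end points, and an analysis plan cannot analyse events that are not collected.

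**Conclusion.** The point holds in a limited form. The two safety end points include nothing specific to a procedure: the marrow puncture is not covered at all, and the infusion is covered for arrhythmia alone. Other serious consequences are counted only as general end points, where they cannot be told apart from the ordinary course of the disease. This is a gap in what the trial can say about safety; it does not affect the efficacy comparison.

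The size is what the trial gives up. Assuming 30 per group, no puncture complications in 60 patients would exclude a true rate above 4.9%, or above 9.5% in one arm of 30 (one-sided 95%). As written, the trial can put no limit on that rate. That the gap exists depends on neither the sample size nor the allocation ratio. It is worth correcting because the correction is cheap.

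**What to change.** Add a third safety end point to the protocol's safety list: in-hospital procedural complications from randomisation to discharge, comprising bleeding or infection at the puncture site, and bleeding, coronary occlusion or dissection from PCI or cell infusion.

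- Record it on the same form in the individual protocol for all three groups. Including PCI complications makes group 3 a fair comparator.
- Report counts by randomised group with exact confidence intervals. Show the puncture items separately, since group 3 has no puncture.
- Report in-hospital re-infarction as a subset of the existing repeated-infarction end point and leave it out of the new item, so that it is not counted twice.
- State the delivery route for the CD133+ cells, so that it is clear how many patients the infusion items apply to.

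The cost is one line in the safety list, about a page in the individual protocol, and slightly more recording. The source data are probably in the hospital chart already, though the protocol does not say so. No treatment changes.
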